Even if the reported benefit on PPC rates is a true effect, it is not known if Pre-Op education and training would be effective in the context of recent advances in perioperative management such as Enhanced Recovery After Surgery (ERAS) guidelines. This multimodal package of 10–18 care elements provides significant improvements in complication rates and LOS [49]. Pre-operative education and lung expansion training are strongly recommended within ERAS guidelines, although it is acknowledged that evidence to support this specific element is weak [50]. Additionally, Pre-Op physiotherapy interventions previously studied were predominantly provided the day before surgery. This may not reflect current practice where, in many centres, patients attend a multi-disciplinary assessment clinic one to 6 weeks before their operation [51–53]. It is unknown whether Pre-Op physiotherapy education provided at these longer time intervals might also produce the previously reported effect on PPC prophylaxis.

Surveys of physiotherapy services to UAS patients in Australia have shown a stark reduction in hospitals (20 % down to 5 %) providing Pre-Op physiotherapy over the past 15 years [34, 54]. The reasons for this disinvestment of services are unknown. There are no cost-benefit analysis studies investigating physiotherapy to reduce respiratory complications, so conclusive evidence to inform the allocation of physiotherapy services to pre-operative education and training is lacking. Additionally, only short-term outcomes have been assessed. Reducing PPCs during the acute hospital stay may also improve important patient-focused longer term outcomes such as health-related quality of life (HRQoL) and physical capacity following discharge.

Considering the relative high incidence of PPCs following major UAS and the benefit to both the patient and the health care system if these were reduced, a well-designed, adequately powered trial is needed to determine both the clinical effect and cost benefit that Pre-Op physiotherapy education and training may, or may not, have on reducing PPC incidence following major UAS. Results will guide future cost-effective allocation of services to patients who require UAS.

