### Trial setting

The three participating centres: the Launceston General Hospital (Launceston, Tasmania, Australia), North Shore Hospital (Auckland, New Zealand), and North West Regional Hospital (Burnie, Tasmania, Australia), represent a range of public hospital types. The North West Regional Hospital is a 240-bed rural secondary referral hospital; the Launceston General Hospital is a 330-bed inner-regional, primary referral hospital; and the North Shore Hospital is a 600-bed metropolitan, primary referral hospital. North Shore Hospital has also implemented Enhanced Recovery After Surgery (ERAS) guidelines to all surgical units. All hospitals are government funded, university affiliated, teaching hospitals.

Patients undergoing elective UAS at the participating centres attend an outpatient Pre-Admission Clinic (PAC) session one to six weeks prior to their operation where they are assessed by a multi-disciplinary team consisting of, as a minimum, a registered nurse, anaesthetist, and doctor from the admitting surgical team. Information about the surgical process, pain management, post-operative drips and drains, and expected recovery process are provided as standard care. Whereas, Pre-Op physiotherapy education and training at PAC is not normally provided, post-operative respiratory therapy and assisted ambulation by a physiotherapist are provided as standard care at the participating centres.

Each participating hospital’s institutional review board has approved the trial (the Human Research Ethics Committee (Tasmania) Network, Tasmania, Australia (protocol reference: H0011911), the Health and Disability Ethics Committee, New Zealand (protocol reference: 14/NTA/233)). The trial is conducted in accordance with the Declaration of Helsinki and was prospectively registered on 19 June 2013 at the Australian New Zealand Clinical Trials Registry (http://www.anzctr.org.au): ACTRN12613000664741.

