### Intervention group

Intervention group participants will be assessed and provided with an information booklet as per the control group and will then receive an additional single education and training session of approximately 30 min with a physiotherapist. Participants will be given an estimate of their likelihood of a PPC based on a risk prediction tool [5] and educated about the effect of anaesthesia, UAS, and bed rest on mucociliary clearance and lung volumes [19, 20]. To ameliorate these factors and prevent bacteria stagnation [15, 16] the importance of participating in an early post-operative ambulation program and performing self-directed DB&C exercises will be emphasised. Participants will be informed that a physiotherapist will assist them to walk as soon as possible on the first post-operative day, aiming for a duration longer than 10 min and at a pace causing mild breathlessness. Outside these assisted sessions, participants will be advised to walk or exercise by their bedside as frequently as they are able.

As it is frequently not possible to ambulate as early and as often as recommended to assist in preventing respiratory complications [8, 60], participants will be educated on the necessity of performing self-directed breathing exercises to protect their lungs following their operation. They will be instructed to perform DB&C exercises immediately from waking from the anaesthetic and then every hour during daytime waking hours until their first ambulation session, and then at any time when they are not ambulant. The physiotherapist will coach each participant in at least three repetitions, and as many as required to master technique as judged by the physiotherapist. This trial’s DB&C exercises consist of two sets of 10 slow-flow breaths to maximum inspiratory capacity with two to three inspiratory sniff breath stacking manoeuvres [61]. Each breath is held for 3 to 5 s. Each set of 10 breaths is followed by three coughs, or a forced expiratory technique with an open glottis called a ‘huff’, with a small firm pillow pressed over on the abdominal incision to support the wound and to encourage greater expiratory force. Participants will be encouraged to practice these exercises prior to their operation to develop familiarity.

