### Secondary trial outcomes

Secondary outcomes (Fig. 2) are:Days of hospital length of stay (LOS). This is defined as the continuous time spent in any type of inpatient hospital service (acute care, sub-acute rehabilitation, and time at another hospital) from the day of admission to the day of discharge to a community dwellingICU LOS in days;Unplanned ICU admission at any time point during the acute stay;Pneumonia, defined as the presence of new CXR infiltrates along with at least two of the following criteria: temperature >38 °C, dyspnoea, cough and purulent sputum, altered respiratory auscultation, and WCC >14,000/ml or leukopenia <3000/ml [65] on any day within the first 14 post-operative hospital days;Time in hours from end of operation to time able to achieve ambulation greater than 1 min;Time in days from end of operation to post-operative day able to achieve ambulation greater than10 min;Time in days to discharge from physiotherapy service (Table 4) [62];Time in days to readiness for discharge from hospital as defined by standardised scoring criteria [66];Hospital costs for the UAS admission episode of care. This will be supplied by the participating centres’ or health departments’ costing data for each participant’s admission episode.Patient-reported complications at 6 to 8 weeks following day of surgery using a standardised semi-structured interview; andHRQoL using the SF-36 and functional capacity using SAQ [58, 67] at 6 to 8 weeks following day of surgery.

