### Statistical methods

The prognostic strength and size of imbalances to potential confounding baseline variables between groups will be assessed. Adjustment covariates will be selected by backward stepwise regression from covariates that may have the potential for clinically significant alterations in effect sizes. These include: history of a respiratory comorbidity, smoking history, self-reported physical activity levels, age, BMI, length in time of operation, operation category (upper gastrointestinal, colorectal, urological, other), ICU admission immediately following the procedure, incision type and location [72], intraoperative ventilation strategies [4, 73], fluid delivery [74], blood transfusions [75], mode of post-operative analgesia [76], and use of prophylactic antibiotics [50].

All outcomes are to be analysed using intention-to-treat. The absolute and relative rates of PPC in the trial groups will be estimated using multivariate robust random effects Poisson generalised linear regression to allow assessment of binary outcomes with or without adjustment for potential confounding variables (incidence rates and rate ratios, 95 % confidence intervals, *P*-values). Treatment centre will be treated as a fixed variable in the multi-level models. In addition, the effect of time from the end of surgery/anaesthesia to commencement of symptoms of PPC will be compared using Cox proportional hazards regression with and without covariate adjustment (hazards ratio, 95 % confidence intervals, *P*-values). Graphic representation of this analysis will be performed using the Kaplan-Meier method.

Binomial secondary outcomes, including pneumonia, unplanned ICU admission, and patient reported complications, will be analysed using mixed effects Poisson regression. Secondary outcomes with irregular distributions, including length of time periods (ICU and total post-operative LOS, time to ambulation for 1 and 10 min, and time to discharge from assisted ambulation physiotherapy service), HRQoL, and functional capacity, will be evaluated for group differences using mixed effects ordered logistic regression, with mean time (95 % CI) estimated for descriptive purposes using mixed effects linear regression, with or without log transformation depending on distribution. Hospital costs associated with the interventions will be compared using mixed effects linear regression. Log transformation of highly skewed cost data will be performed.

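### If costs are skewed, the planned log-scale comparison is of geometric means, and the admission-only cost leaves out the pre-operative session, so the plan gives neither the mean nor the net cost that its cost-benefit rationale needs

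*Protocol article*

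**What the plan says.** **Aim.** The Background calls for a trial to "determine both the clinical effect and cost benefit that Pre-Op physiotherapy education and training may" (or may not) have on PPC incidence, and expects the results to guide where services are placed cost-effectively. The formal secondary objective, under Trial objectives, is narrower: hospital costs.

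**Outcome.** Secondary trial outcomes defines it as "Hospital costs for the UAS admission episode of care", supplied by the centres or health departments as "costing data for each participant’s admission episode".

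**Analysis.** Statistical methods states: "Hospital costs associated with the interventions will be compared using mixed effects linear regression". It continues: "Log transformation of highly skewed cost data will be performed". For the time outcomes the same paragraph adds an estimated mean with a 95% confidence interval. For costs it names no mean and no return from the log scale.

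**Intervention.** Patients "attend an outpatient Pre-Admission Clinic (PAC) session one to six weeks prior to their operation". Both arms receive the assessment and the booklet. The intervention arm also receives an "additional single education and training session of approximately 30 min with a physiotherapist". Trial setting notes that "Pre-Op physiotherapy education and training at PAC is not normally provided". Under Standardisation of pre-operative interventions, a wait of more than 42 days triggers a telephone review in both arms, and the intervention arm then has the education and exercises repeated.

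**The concern.** There are two separate problems.

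1. **Scale.** A payer's total spend is the arithmetic mean cost times the number of patients. A linear model on log cost estimates a ratio of geometric means. The two ratios agree only if costs have the same spread and shape on the log scale in both arms. If the session works as hypothesised, it removes some expensive PPC admissions, so the arms will differ in exactly that part of the distribution, which the log scale down-weights.

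2. **Scope.** The main planned difference in resources between the arms is the extra session, and it takes place before the admission. A cost defined by the admission episode therefore gives the intervention a cost of zero. The error can run only in the intervention's favour. The phrase in Statistical methods about costs associated with the interventions could be read as including the session, but the outcome definition does not include it. The two sections need reconciling.

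At stake is whether the reported cost result can support a statement about mean or net cost per patient.

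**Working it through.** The article states no cost figure, so there is nothing of its own to reproduce. The calculation below is an illustration.

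**Inputs from the protocol.** PPC 20% (booklet) and 10% (session), from Sample size; session about 30 minutes, from Intervention group; 441 participants, so about 220 per arm.

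**Assumed inputs.** Cost is lognormal; a PPC multiplies median cost by *m*; log-SD is *s* = 0.5 without a PPC and *s*ₚ with one.

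**Formulas**, with *p* the PPC rate:
- arithmetic mean ∝ (1 − *p*)·exp(*s*²/2) + *p*·*m*·exp(*s*ₚ²/2)
- geometric mean ∝ *m*^*p*

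**Equal spread, *m* = 2.** Arithmetic ratio = 1.1/1.2 = 0.917, a saving of 8.3%. Geometric ratio = 2^0.1/2^0.2 = 0.933, a saving of 6.7%.

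**PPC costs more variable, *m* = 2, *s*ₚ = 0.8.** exp(0.125) = 1.133 and exp(0.32) = 1.377.
- Session arm: 0.9 × 1.133 + 0.2 × 1.377 = 1.295
- Booklet arm: 0.8 × 1.133 + 0.4 × 1.377 = 1.457
- Arithmetic ratio 0.889, a saving of 11.1%; the geometric saving stays at 6.7%.

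| *m* | Geometric saving | Arithmetic, *s*ₚ = 0.5 | Arithmetic, *s*ₚ = 0.8 |
|---|---|---|---|
| 1.5 | 4.0% | 4.5% | 7.1% |
| 2 | 6.7% | 8.3% | 11.1% |
| 3 | 10.4% | 14.3% | 17.3% |

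Across these cases the log scale shows between 56% and 87% of the proportional saving in mean cost.

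**Limiting case.** With equal geometric means and log-SD 0.8 against 0.6, the log model targets no difference. The arithmetic ratio is exp((0.36 − 0.64)/2) = 0.869, a 13% difference in mean cost.

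**Session input.** 0.5 h × 220 ≈ 110 physiotherapist hours across the intervention arm. On the protocol's rates, 1/(0.20 − 0.10) = 10 sessions, or 5 hours, are spent per PPC avoided, before telephone repeats. No pay rate is given. At an assumed 50 to 100 currency units per hour the session costs 25 to 50 per participant.

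**The case against.** Much of the opposing case stands.

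- **The formal objective is hospital costs**, and the outcome definition agrees with it. A reader might infer that the trial fails a declared cost-benefit endpoint. No such endpoint is listed; the cost-benefit language is rationale in the Background. The gap is between that rationale and the planned analysis.
- **The log step is conditional** on high skew. Without it, the stated model compares arithmetic means. An analysis plan that is not shown might also convert log-scale results back to mean cost. But skew is likely in surgical admission costs, and the article sets the log model as the response to it.
- **A reader might infer that the log model halves the saving.** In a simulation with median cost 20,000, log-SD 0.5, a PPC doubling cost and PPC costs more variable, arithmetic means were 28,947 and 25,847 (difference 3,100) and geometric means 22,965 and 21,446 (difference about 1,500). Those are differences on unlike scales. A log model estimates a ratio, and the same figures give savings of 10.7% and 6.6%.
- **Nor does the log model miss a saving that raw cost would find.** With these inputs, 220 per arm and Welch tests, power is about 28% on raw cost against 22–23% on log cost (19–20% against 16% at log-SD 0.7). Either scale would usually miss it. The issue is what is estimated. A reversal of sign is possible in principle, but the PPC scenarios worked here do not show one.
- **The session cost is small.** At the assumed pay rates it is 0.8–1.6% of the 3,100 difference, and it is nearly constant, so it could be subtracted afterwards. That bears on its size; the stated definition still excludes it.

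**Conclusion.** The point holds in limited form. If costs are highly skewed, the planned comparison is of geometric means, and the admission-only definition omits the session. As written, the plan therefore yields neither the arithmetic mean difference nor the net cost that the Background's aim needs. With PPC at 20% and 10% and a PPC doubling cost, the understatement of the proportional saving is modest with equal log spread (6.7% shown against 8.3%) and larger if PPC costs are more variable (6.6–6.7% against about 11%). These sizes rest on assumed cost distributions, because the documents contain no cost data. The missing session cost is small and its direction is known. The primary outcome and the other secondary outcomes are untouched.

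**What to change.** 1. **Target.** State that the cost estimand is the difference in arithmetic mean cost. Estimate it by a gamma GLM with log link and marginal means, or by regression on untransformed cost with a bootstrap interval. Enter centre as a fixed covariate, as the article already intends for its multi-level models, and express Australian and New Zealand costs in one currency. Keep log cost as a sensitivity analysis.
2. **Scope.** Add a nominal session cost to each intervention participant: about 30 minutes, plus any telephone review, at pay rates for the physiotherapist's grade. The article plans to report grade and the number of participants each physiotherapist sees, and to record mode of delivery. It does not list session duration as collected, so the costing must use the nominal time unless a duration field is added. Otherwise, describe the result as admission cost only and make no net-cost claim.
3. **Wording.** Align the cost phrase in Statistical methods with the definition in Secondary trial outcomes.

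The cost is a change of analysis wording and one multiplication per participant. The downsides are somewhat wider intervals than on the log scale and a slightly smaller net saving.

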### Data monitoring

The steering committee consists of the principal investigator and three academic supervisors who contribute to design and revision of the study protocol. The principal investigator is responsible for study administrative management and communication with local investigators, and for assisting participating centres with trial conduct, record keeping, and data management. An independent Data and Safety Monitoring Board (DSMB) consisting of a senior academic, staff anaesthetist, and biostatistician monitors the ethics of the study in accordance with the Declaration of Helsinki, overseeing safety and conduct of the study. This study compares two education-based treatment strategies that are highly unlikely to be related to serious adverse events (SAEs), though local investigators at participating centres remain responsible for reporting SAEs directly attributable to the intervention or control to the DSMB for review and consideration for referral to the institutional ethics review board.

### Duration and timeline

All 441 patients will be recruited by October 2015. Data collection will be completed, analysed, and the manuscript prepared for submission by March 2016. The final manuscript will be written in accordance with the CONSORT extensions for a pragmatic trial using a non-pharmacological intervention.

## Discussion

Studies in major UAS that have used the same PPC diagnostic tool as our group have reported a PPC rate of 13–18 % across all types of UAS [5, 6] with a specific rate of approximately 40 % in high-risk patients [8, 9]. Due to high incidence rates and costs of PPCs to patients and health care systems, there is great interest in their prevention.

Several clinical trials have compared a variety of different types and combinations of interventions to prevent PPCs. Trials demonstrating improvements in PPC rates have used multimodal interventions, so it is difficult to determine which component is effective in reducing PPCs, or indeed, if it is necessary to provide the whole ‘package of care’ to gain a significant benefit. This may influence resource provision, as providing the full package of therapy exactly as studied to gain the reported reduction on PPC rates may not be feasible, could be costly, and, indeed, may not be necessary in its entirety. Previous clinical trials have demonstrated that a single pre-operative education session can reduce PPC incidence to as low as 6 %, compared to a no-treatment control group rate of 27 %, *P* < 0.001 [47, 48], though assessors were un-blinded and potential confounders were not reported. Further, these trials were conducted 10–15 years ago, and changes in surgical and perioperative care have been significant in this time. The potential to significantly reduce the incidence of a high impact complication such as a post-operative respiratory complication with a low-cost and easily provided intervention of a single pre-operative physiotherapy session is appealing. It may not be ‘how much’ physiotherapy that is important, but rather ‘when’ that physiotherapy is provided. Unfortunately, conclusive evidence to support this hypothesis is lacking.

The LIPPSMAck POP trial is the first randomised controlled study powered and designed to investigate whether Pre-Op education and training reduces the incidence of PPCs. This RCT has been specifically designed to address previous methodological shortcomings in clinical trials investigating this intervention. Eligible participants are all patients listed for elective upper abdominal surgery and are representative of the heterogeneous nature of patients listed for these procedures. To ensure generalisability of results, the intervention will be delivered pragmatically and reflect current service delivery in Australia and New Zealand. Pre-operative education will be provided by a range of physiotherapists with different experience levels, including supervised students. The intervention and control has been designed and standardised to be provided by a physiotherapist of any experience level.

The active control of being assessed by a physiotherapist and receiving an identical subjective and objective interview and booklet, was chosen instead of a no-treatment comparator to specifically control for the Hawthorne effect. The LIPPSMAck POP trial standardises assisted early ambulation services and removes all physiotherapy coached respiratory therapy and provision of lung expansion devices post-operatively. We have not attempted to control for ambulation initiated by the participant or lung expansion exercises provided by nursing or medical staff and, in practice, this would be extremely difficult to achieve. However, with effective random allocation and blinding of post-operative staff members, it is reasonable to expect that patients in both the control and the intervention group will have an equal chance of having similar exposure to these factors. Regarding other known confounders such as pain management strategies, fluid administration, and intraoperative ventilation strategies, we have not attempted to standardise these due to the feasibility of doing so across three sites. Instead, the impact of potential perioperative confounders will be evaluated during statistical analysis and reported.

The primary outcome, PPC, will be measured by assessors masked to group allocation; all post-operative ward staff responsible for the delivery of all physiotherapy, medical, nursing, and general care and discharge planning will also be masked. The success of blinding procedures will be measured and reported. In modern health care delivery it is also important to consider the impact of an intervention on patient reported quality of life and not just on objective clinical outcomes [77]. It is hypothesised that if Pre-Op physiotherapy education is effective in reducing the incidence of a PPC, this may improve post-surgical recovery. Improvements in recovery may influence HRQoL following discharge from hospital, particularly physical functioning domains, as has been demonstrated previously [59]. LIPPSMAck POP will be measuring 6-week post-discharge patient reported complications, HRQoL, and functional capacity to estimate the potential effect that PPCs may have on these outcomes.

In conclusion, the LIPPSMAck POP trial is an investigator-initiated, bi-national, multi-centre, pragmatic, double-blinded, randomised controlled trial, powered and rigorously designed to test the hypothesis that pre-operative physiotherapy education prevents post-operative pulmonary complications in patients following major upper abdominal surgery.

